## Abstract

**Introduction:**

Sub-Saharan Africa loses up to 50% of fruits and vegetables produced annually, with Ghana alone reporting post-harvest losses ranging between 30 and 50% across the value chain. These losses significantly threaten nutrition security by reducing the availability of essential nutrients in the food system. Capturing these lost nutrients is crucial to promoting healthy and affordable diets. This study protocol presents a community-based randomised controlled trial (RCT) being implemented in the Ho West District of Ghana. The trial aims to investigate the association between post-harvest loss (PHL) of fruits and vegetables and the nutritional status of women and children, while also identifying loss drivers across the value chain.

**Methods:**

This experimental trial study employs an untreated control group design and involves 280 participants, comprising 70 farmers, 70 traders, and 140 women and their children. Socio-demographic data and post-harvest practices will be collected from all participants to estimate nutritional losses. Dietary intake of fruits and vegetables will be assessed using food frequency questionnaires, while food consumption and household hunger will be measured using validated scoring tools. Anthropometric and nutritional measurements will be recorded for women and children using WHO protocols. Women in the intervention arm will receive nutrition education and counselling focused on storage and preservation strategies to reduce food waste.

**Potential impact:**

This study will provide evidence on the link between post-harvest loss and nutritional outcomes and inform practical interventions for reducing PHL at the community level. It offers a platform for building capacity among farmers, traders, and caregivers through increased awareness and behaviour change. By integrating nutrition education into PHL mitigation, the findings have the potential to influence food systems policy, improve household nutrition, and contribute to global efforts to reduce food loss. The trial is currently ongoing, and this protocol outlines the study’s design, methodology, and implementation framework.

**Clinical trial registration:**

This trial is registered with the Pan African Clinical Trial Registry (PACTR202310582275172).

## Introduction

Post-harvest loss (PHL) is defined by the Food and Agriculture Organisation (FAO) as the measurable reduction in both the edible mass (quantity) and nutritional value (quality) of food intended for human consumption (1). The post-harvest system includes several interconnected processes that begin at harvest and extend through processing, marketing, preparation, and ultimately, household consumption. At each of these stages, substantial food losses occur globally, resulting in decreased food availability and accessibility (2, 40).

Globally, an estimated one-third (1.3 billion tonnes) of food produced for human consumption is lost or wasted annually (1). These losses are particularly severe in developing countries, where they can lead to income reductions of at least 15% for an estimated 470 million smallholder farmers and others along the food value chain (3, 4). Most of these losses are attributed to food loss along the value chain, which accounts for approximately 90% of total waste (5). This has far-reaching implications for food prices, food security, and nutritional health (38).

In Sub-Saharan Africa and other low-income regions, plant-based foods form the key source of household diets, supplying nearly 90% of daily energy and 80% of protein requirements (5). However, these food categories, including grains, fruits, vegetables, legumes, and tubers, represent up to 92% of all post-harvest losses in the region. Among them, fruits and vegetables experience the highest losses, with estimates suggesting that nearly 45% are discarded or wasted before reaching consumers (6, 7).

Post-harvest loss of fruits and vegetables is a significant concern for achieving food security and reducing global hunger (8, 9). In Ghana, approximately 30–50% of fruits and vegetables are lost along the entire value chain (10–12). These losses occur at different stages, including harvesting, handling, storage, and retail. A study in Ethiopia showed that post-harvest handling, storage, and marketing account for 85.6, 11.6, and 2.8% of total losses, respectively (46, 48). As a result, there is a decreased availability of essential, nutrient-rich foods, especially for vulnerable groups such as women and children, who have high nutritional needs (13). The shift towards less nutritious, processed, or starchy foods due to limited access to fresh produce further worsens micronutrient deficiencies (14, 15).

This study addresses a critical public health issue: the extent to which post-harvest losses of fruits and vegetables contribute to nutritional deficiencies in women and children. A growing body of data supports the underlying causes of nutritional deficiencies. However, understanding a long-term solution to this enduring issue would require considering the complex interactions between agricultural and health factors, especially through nutrition-sensitive agricultural interventions that simultaneously address food system and health challenges (16). While many studies have examined PHL at the farm and retail levels (11, 17, 18), few have explored its magnitude and nutritional implications at the household level (19). Moreover, there remains a lack of systematic evidence examining the direct relationship between post-harvest losses and nutritional outcomes.

This study tackles a significant gap in understanding how post-harvest losses of fruits and vegetables contribute to nutritional outcomes among women and children in low-resource rural areas. While earlier research has looked at losses at the farm or retail level, few have focused on household-level losses or directly connected them to measurable nutritional outcomes. Therefore, this study presents a community-based intervention study aimed at estimating post-harvest losses along the value chain and assessing their impact on the nutritional status of women and children. It also aims to determine how structured nutrition education and counselling can minimise losses and enhance nutritional outcomes, thereby directly addressing the identified issue. By engaging key actors along the value chain and households, this study contributes to ongoing efforts to strengthen food system resilience, public health, and nutrition security.

## Study objectives

The primary objective of this study is to investigate the relationship between post-harvest losses of fruits and vegetables and the nutritional status of women and children in the Ho West District of Ghana. Specifically, the study aims to estimate the extent and drivers of post-harvest losses at the farm, retail, and household levels, to determine the nutrient losses associated with post-harvest waste of fruits and vegetables, to examine the relationship between the nutritional status of women and children in households and fruits and vegetables losses and to evaluate the effect of a structured community-based nutrition education and counselling intervention on post-harvest practices, fruit and vegetable consumption, and nutritional outcomes.

## Research design and methods

### Study setting

The study will be conducted in the Ho West District of the Volta Region in Ghana. The Ho West district shares borders with the Republic of Togo, and its capital, Dzolo-Kpuita, is located 175 km northeast of Accra. The total population is 95,000 (20). Anaemia and undernutrition remain critical public health issues in this region. Recent national trends indicate that anaemia prevalence among children under 5 years, although decreasing, remains alarmingly high at 48.9% as of 2022, down from 76.1% in 2003 (21). In the Volta Region specifically, hospital-based data shows that over 55% of children under five are anaemic (22). Stunting, a marker of chronic undernutrition, also affects nearly one in five children under five in Ghana (23). In the Ho West district, 73.5% of the people work in agriculture in some capacity. Less than 1 % (0.06%) of households involved in agriculture are involved in fish farming, with the majority (95.2%) in crop farming (47). Farmers in this region cultivate a diverse range of fruits and vegetables, including bananas, pineapples, mangoes, pears, and oranges. These four farming communities, Abutia Kissiflui, Dededo, Amedzofe, and Kpedze, will be the focus of the study. The district’s busiest market, located in Abutia Kissiflui, generates up to 75% of the district’s tax revenue. Contributions from Dededo, Amedzofe, and Kpedze are 12.3, 8.7, and 4%, respectively. Kpedze has a population of 4,692 people, of which 12% are children under the age of five and 51% are women. There are 3,360 people living in Dededo, 16% of whom are children under five, and 53.3% of whom are women. A total of 1,561 people reside in Amedzofe, with 51.2% of them being women and children. With 1,667 residents, Abutia Kissiflui has a female population of 54% and a child population of 13.5% (20, 24). The district’s southernmost neighbourhoods, Kpedze and Amedzofe, were selected for the intervention group, while the northernmost neighbourhoods, Dededo and Abutia Kissiflui, were designated as the control group. Out of the 14 towns in the district, these towns were specifically chosen. To prevent contamination, the control and intervention groups were selected based on their proximity to one another and their geographic location. Also, data on nutritional treatments and services provided in each group will be recorded.

### Study design

The study is an experimental trial with an untreated control group, adhering to the Consolidated Standards of Reporting Trials (CONSORT). The study will be conducted in three main phases: Phase I (problem identification and quantification), Phase II (intervention development and implementation) and Phase III (evaluation of intervention). The outcome of the study will be assessed twice, at baseline and post-intervention. The intervention will be tested on households, which will receive structured education on fruit and vegetable intake, as well as methods for waste and food preservation. Women in the household will be educated on food preservation methods and how to store various types of fruits and vegetables at home. They will receive intervention for 6 months.

### Study duration

The study will have a total duration of 16 months. Recruitment of participants will last for 1 month. Data collection on anthropometric indices, blood samples, and dietary intake will be conducted over 3 months. The intervention phase will last for 6 months. A duration of 3 months will be used for the statistical analysis and final write-up.

### Study status and timeline

This protocol outlines a community-based randomised intervention study aimed at improving nutritional outcomes and reducing fruit and vegetable waste. The study commenced on 1st August 2024 and is expected to conclude on 31st July 2025. At the time of this submission, Participant recruitment has been completed, and data collection is ongoing, with plans to continue through to 31 July 2025. Data analysis and result generation will commence after the conclusion of data collection, with preliminary results anticipated by September 2025. No results have been generated or analysed prior to this submission. The study timeline, including enrolment, intervention, and assessment time points, is presented in Figure 1 following the SPIRIT guidelines (SPIRIT 2013 Statement).

**Figure 1 fig1:**
[figure not shown]
SPIRIT schedule of enrolment, interventions, and assessments [Adapted with permission from Chan et al. (49)].

### Sampling

A multistage sampling approach will be employed to select study participants. First, the Ho West District in the Volta Region of Ghana will be purposively selected due to its significance in fruit and vegetable production, retail activities, and rural household participation. Second, the district will be stratified geographically into northern and southern zones. From each zone, two communities (Amedzofe and Kpedze in the north; Abutia-Kissiflui and Dededo in the south) will be purposively selected based on agricultural diversity and accessibility.

From each of the four selected communities, farmers and traders will be randomly selected for the study. Systematic random sampling will be used to select households. A household list will be obtained with the assistance of community health volunteers or local authorities. Using a random start, every *nth* household will be selected. In each selected household, eligible participants, defined as women of reproductive age (with a child under five), will be invited to participate.

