### Statistical analysis

Statistical package for social sciences (SPSS) (IBM Corp. Released 2022. IBM SPSS Statistics for Windows, Version 30.0. Armonk, NY: IBM Corp) will be used for the data analysis. The Kolmogorov-Smirnov and Shapiro-Wilk tests will be used to assess the normality of the quantitative data. A *p*-value less than 0.05 indicates that the data is not normally distributed, and vice versa. The characteristics of the study participants will be analysed using descriptive statistics. A chi-square test will be done to assess the relationship between categorical variables. Fisher’s exact test will be employed to determine the significance level. Parametric tests will be used to analyse normally distributed data, and non-parametric tests will be used to analyse data that is not normally distributed. Parametric tests will be presented in terms of mean and standard deviation, and non-parametric tests will be presented in terms of median (maximum-minimum). A t-test will be conducted to compare the mean differences of the outcomes of interest within and between study groups at baseline and post-intervention. Regression analysis will be conducted to predict the drivers of fruit and vegetable loss, adjusting for age and gender. Partial correlation will be used to assess the strength of association among the variables. All *p*-values will be significant at *p* < 0.05.

The primary analysis will follow the intention-to-treat (ITT) principle, including all participants as initially allocated, regardless of their adherence to the intervention protocol. This approach ensures an unbiased estimate of the intervention effect. For secondary per-protocol analyses, only participants who fully adhered to the intervention will be considered. To address missing data, particularly in outcome measures such as dietary assessments and anthropometry, multiple imputation methods will be employed under the assumption that data are missing at random. Sensitivity analyses will be conducted to assess the robustness of results. This strategy helps maintain the validity and reliability of findings despite potential data gaps.

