To account for multiplicity in the analysis of primary and secondary outcomes, the study will employ a structured analytical approach. Primary and secondary outcomes will be pre-specified to avoid *post hoc* comparisons. Where outcomes are assessed at multiple time points (e.g., baseline and post-intervention), repeated-measures analysis or appropriate statistical corrections such as the Bonferroni adjustment will be applied to control the risk of Type I error. Subgroup analyses (e.g., by community or demographic characteristics) will be exploratory and clearly labelled as such to prevent overinterpretation. These steps ensure robust and reliable interpretation of findings while maintaining the statistical integrity of the study. This protocol was developed in consultation with a statistician. The statistician reviewed sample size estimations and the statistical analysis plan to ensure methodological soundness. This is reflected in the detailed statistical analysis section, which outlines methods for dealing with missing data, baseline comparability, and outcome estimation.

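### The loss-driver regression adjusts only for age and gender although its data are pooled from four unlike communities, so community differences can be mistaken for farm- or household-level drivers.

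*Protocol article*

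**What the plan says.** The Sampling section describes purposive choice of the district and of four communities, then sampling within them: "From each of the four selected communities, farmers and traders will be randomly selected for the study". Households are drawn from the communities by systematic sampling.

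Study setting shows how unlike the four places are. The market "located in Abutia Kissiflui, generates up to 75" per cent of the district's tax revenue; for the other three, "Contributions from Dededo, Amedzofe, and Kpedze are 12.3, 8.7, and 4%, respectively". On size, "Kpedze has a population of 4,692 people", while the others have 3,360, 1,667 and 1,561.

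Study objectives lists the extent and drivers of loss at farm, retail and household level, and also aims "to examine the relationship between the nutritional status of women and children in households and fruits and vegetables losses".

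Statistical analysis gives the methods for these aims in two sentences: "Regression analysis will be conducted to predict the drivers of fruit and vegetable loss, adjusting for age and gender", and "Partial correlation will be used to assess the strength of association among the variables". The first names its covariates; the second names none. The section's only other use of community is this: "Subgroup analyses (e.g., by community or demographic characteristics) will be exploratory and clearly labelled as such to prevent overinterpretation". The article states no community term, mixed model or cluster-robust standard error.

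**The concern.** When observations are pooled over a few communities without a community term, the slope of loss on a candidate driver is a blend. One part is the relation among farms or households in the same community. The other is the line through four community means. The usual standard error treats every farm or household as an independent observation of both parts, whereas the second rests on four points.

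The direction of the bias is not predictable. As a hypothetical example, a market town with both more loss and more varied diets would give a positive loss-diet association even if no such relation held between households within any community. Drivers of loss and the loss-nutrition relation are stated objectives, so a false lead here would reach the study's main conclusions.

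This is a different question from the comparison of intervention and control. There, each community lies wholly in one arm, so community indicators would absorb the arm contrast. Here the exposure is a characteristic of a farm, trader or household that varies within communities, so indicators cause no such difficulty. If post-intervention data are pooled, they also remove the part of the association that is due to arm.

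**Working it through.** **Inputs from the protocol.** Four communities; 140 households; a total of 70 set for farmers and market vendors; 5% level; driver regression adjusted for age and gender.

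**Assumptions, not in the protocol.** Equal split over communities: 140/4 = 35 households, and 70/4 = 17.5, taken as 17 farmers or traders. ICC of driver (ρx) and of outcome (ρy): 0 to 0.20 when equal, and up to 0.8 for a driver that is largely a community trait. Two-sided test.

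**The plan's own figure.** The 70 comes from a single-proportion calculation at 20%, with no precision given. With an assumed ±10 points, 1.96² × 0.2 × 0.8 / 0.1² = 61.5, so 62; then 62/0.9 = 68.9, so 69, close to 70. This only sets the number per community; the point does not depend on it.

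**Hand approximation of the error.** With m per community, the variance of a pooled slope is understated by about D = 1 + (m − 1)ρxρy. The true error of the 5% test is then about 2[1 − Φ(1.96/√D)].

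- m = 35, ρx = ρy = 0.05: D = 1 + 34 × 0.0025 = 1.085; error 6.0%.
- m = 35, both 0.10: D = 1.34; error 9.0%.
- m = 35, both 0.20: D = 2.36; error 20%.
- m = 35, ρx = 0.8, ρy = 0.05: D = 2.36; error 20%. With ρy = 0.10: D = 3.72; error 31%.

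This overshoots somewhat with only four communities, so simulation is the better guide.

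**Simulation.** Random community effects on driver and outcome, no relation within communities, 20,000 runs per setting. The pooled correlation test is compared with the same test after community means are removed, which is equivalent to three indicator terms.

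| ρx, ρy | Pooled, 4 × 35 | Pooled, 4 × 17 |
|---|---|---|
| 0.01, 0.01 | about 5% | about 5% |
| 0.05, 0.05 | about 6% | 5 to 6% |
| 0.10, 0.10 | about 8% | about 6% |
| 0.20, 0.20 | about 16% | 10 to 11% |
| 0.8, 0.05 | 17 to 18% | about 11% |
| 0.8, 0.10 | about 28% | 17 to 18% |

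With community removed, the error stays near 5% in every row.

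**Price in power.** Take a slope equivalent to r = 0.24 at n = 140, with no community effect on the outcome. Counting only the lost degrees of freedom (138 against 135), power is 82.8% either way. That count leaves out the between-community variation in the driver, which the indicators discard. The noncentrality is about r√[136(1 − ρx)/(1 − r²)], where 136 = 4 × 34.

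- ρx = 0: 0.24 × √(136/0.9424) = 2.88; power Φ(2.88 − 1.96) = 82%. Simulated: 81%.
- ρx = 0.1: 2.74; 78%. Simulated: 76 to 77%.
- ρx = 0.5: 2.04; 53%. Simulated: 52%, against 74% pooled.
- ρx = 0.8: 1.29; 25%. Simulated: 25%, against about 66% pooled.

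**The case against.** **The loss-nutrition half rests on silence.** A partial correlation controls for something, and a condensed article may leave the list to the analysis plan. A reader might infer that community enters no model at all. The documents do not support that: community is left out of a stated list only for the driver regression. For the partial correlations its absence is not an exclusion. This stands, and it is why the point is anchored on the driver regression.

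**The inflation may be trivial.** No ICC is given, and tax shares and population say nothing directly about loss or diet. At ICC 0.05 or less in both variables the pooled test is close to nominal. This also stands. The documents show that communities can be mistaken for drivers, not that they will be.

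**The largest error rates belong to drivers that the plan does not name.** The variables listed for collection are mostly personal or household ones, such as education, income, storage and routines. For a driver fixed within a community, simulated error at n = 140 is higher still (about 23 to 36% at outcome ICC 0.05 to 0.10). A community term does not repair that test; it removes it. Those figures should not be read as the error that the fix corrects.

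**Differences between communities may be real drivers.** The objectives speak of farm, retail and household levels, and a contrast within communities is not the only legitimate target. That is fair, but four purposively chosen places cannot separate one community trait from another, so such drivers are better described than tested.

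**Subgroup analysis by community is planned.** It is exploratory and leaves the pooled coefficient unchanged.

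**Conclusion.** The point holds for the driver regression. The protocol states a covariate list that is inadequate for a sample pooled from four unlike communities, so this is a method fixed badly and not a detail left out. For the loss-nutrition partial correlations it is a recommendation to name community among the controls.

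The size depends on assumed ICCs and an assumed equal split. For drivers that vary mainly among farms or households, it runs from negligible to about 16% true error at a nominal 5%. For drivers that are mostly community traits (driver ICC 0.8, outcome ICC 0.05 to 0.10), it is about 17 to 28% at n = 140.

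A reader might also conclude that the remedy is free because three degrees of freedom cost almost no power. That is true only for drivers that barely cluster, which is also where the pooled test is nearly correct. For clustered drivers the loss of power is real.

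**What to change.** In Statistical analysis, extend the covariates of the driver regression from age and gender to age, gender and community, with community entered as three indicator terms. State that community is among the controls of the partial correlations between loss and nutritional status. Report drivers that are constant or nearly constant within a community descriptively across the four communities, without a p-value.

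No new data are needed, since each participant's community is known from the sampling. The protocol says no results had been generated at submission, so the change can be dated before analysis.

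The cost is three degrees of freedom, plus the power loss shown above for drivers that vary mainly between communities (for r = 0.24 at n = 140, from about 81% at driver ICC 0 to about 52% at 0.5). The article should say plainly that four communities cannot support tests of community-level drivers.
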